### **Study type**

Phase one will be a hypothesis generating study that concerns with determining the incidence of NVAf and the epidemiology of the under-prescription of anticoagulants in NVAf patients in England. Phase two and three are hypothesis testing studies, that involves the use of data obtained from phase one to make statistical decisions about the associations of prescribing OACs or restarting OACs after MB with developing the predefined clinical outcomes.

### **Study design**

The first phase of this study will be a large population-based cohort study to identify incident cases of NVAf between January 1st, 2009 and 30th of June 2019; to determine the proportions of NVAf patients who have received a prescription for OACs or no treatment; to examine predictors of OACs prescribing. Given the described study aims and objectives, this study design will allow for a longitudinal analysis of incident NVAf cases and the subsequent timing of OACs prescribing with no comparator groups.

The second phase will be a comparative cohort study that aims to compare the clinical outcomes of NVAf based on their exposure status to anticoagulation therapy. Both patient groups will be identified from phase one and further divided into comparative groups of patients who have been prescribed OACs and patients with no anticoagulation therapy. The comparison will be undertaken after controlling for factors that could influence a patient's exposure to OACs and the outcomes to be explored, more details provided in section M.

Finally, the third phase of this study will be a separate analysis of the treatment group from phase two who have experienced major bleeding events. This study design is suitable for this phase as it will allow for a longitudinal analysis of NVAf patients from the indexed bleeding events and onward to evaluate the clinical outcomes (i.e. stroke, bleeding reoccurrence and mortality) related to OACs resumption or not and the timing of restarting OACs after the bleeding event, it will also allow for post-haemorrhage assessment of stroke and bleeding risk using different risk scores, and the identification of predictors for not resuming anticoagulation therapy.

### **Feasibility counts**

Earlier reports on AF prevalence in England estimated that 2.5% of the population have AF for both valvular and non-valvular AF (NVAf), with increasing prevalence in older age-groups. A previous study, that used CPRD GOLD to identify incident cases of NVAf, identified around 91,000 cases from 2001 to 2013. We conducted a simple feasibility count for incident cases of NVAf patients in CPRD GOLD, and we identified at least 120,000 incident cases are expected for the period (2009-2019) with an annual average of around 11,000 new cases. According to a previous study in the UK that estimated the proportion of AF patients at risk for stroke but did not receive either OACs or antiplatelets to be around 12% of total AF cases. Therefore, we expect to identify around 14,000 NVAf patients not treated with OACs across the duration of the study

### **Sample size considerations**

Due to the comparative nature of the second phase of this study, a sample size calculation was undertaken to provide an estimate of the number of cases needed for the second phase of this project (the comparative cohort), and to detect a difference in the major outcomes of interest (ischemic stroke, mortality, or bleeding) between OACs exposed and not exposed NVAF patients. Power calculations were based on stroke within a year of NVAF diagnosis since it is our primary outcome of interest. An Earlier study showed a yearly stroke incidence ranging of 8% with no OACs and 2.8% in patients treated with warfarin. We have assumed an alpha level (two-tailed) of 0.05, a beta of 0.2 (80% power), and a ratio of 5:1 for the OACs exposed-to-unexposed ratios in the matched cohort to detect a relative risk of 2.8 for the dichotomous endpoint (i.e. stroke). This would require a minimum sample number of 970 of patients in OACs treated patients and 194 patients in OACs unexposed patients, giving a total of 1164 patients. Thus, we estimate to have many times the needed numbers in the two databases.

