### Outcomes:

The primary outcome is the composite of ischaemic stroke and other thromboembolic events, or the occurrence of MB events defined according to the ISTH criteria (described in detail in Section D). Secondary outcomes will include CRNMB events that did not satisfy the ISTH criteria and led to hospitalization, medical or surgical treatment, or led to discontinuation of OACs. All outcomes will be identified over the course of follow-up through the identification of corresponding Read codes in patients’ records. For bleeding events since CPRD does not state the number of transfused blood units, any need for blood transfusion along with a Read code for bleeding will be classified as a MB event. Stroke or bleeding events will be identified through Read codes in patients primary care records and through linkage to inpatient HES ICD-10 codes in case of hospitalization secondary to stroke or bleeding. ONS mortality data will be used to ascertain specific causes of death (i.e. bleeding related, cardiovascular, or all-cause death) according

ICD-10 codes. All codes relevant to these outcomes are listed in Appendix 3.

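### The stated minimum of 970 exposed and 194 unexposed patients does not follow from the protocol's own inputs (152/760 does), and the outcome it is sized on needs reconciling with the Phase 2 primary outcome

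*Protocol*

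**What the plan says.** Under Sample size considerations, the Phase 2 comparison is sized on a yes/no stroke endpoint at one year. The event rates come from an earlier study: "An Earlier study showed a yearly stroke incidence ranging of 8% with no OACs and 2.8% in patients treated with warfarin". The error rates are given as "We have assumed an alpha level (two-tailed) of 0.05, a beta of 0.2 (80% power", and the allocation as "a ratio of 5:1 for the OACs exposed-to-unexposed ratios in the matched cohort". The target effect is a relative risk of 2.8. The result is: "This would require a minimum sample number of 970 of patients in OACs treated patients and 194 patients in OACs unexposed patients", a total of 1164. No formula, continuity correction or allowance for losses is named. The section closes by saying that the two databases should supply many times these numbers. Feasibility counts expects about 14,000 untreated patients.

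On the outcome, the same section says: "Power calculations were based on stroke within a year of NVAF diagnosis since it is our primary outcome of interest". The Phase 2 outcomes under Exposures, outcomes and covariates say: "The primary outcome is the composite of ischaemic stroke and other thromboembolic events, or the occurrence of MB events". Outcomes to be measured names the same elements for Phase 2, but without the word composite.

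**The concern.** The section gives every input needed to rebuild the sample size, so the result should come back from them. It does not. With unequal allocation it matters which arm carries the higher rate: the small unexposed arm is assigned 8% and the five-times-larger exposed arm 2.8%, and exchanging them changes the answer by more than a quarter. A reader who checks the figure cannot tell whether the rates, the ratio, the power or the method differs from what is written.

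The second matter is which outcome the power refers to. Study type describes Phase 2 as hypothesis testing. One section treats stroke as primary, and another joins stroke and thromboembolism with major bleeding. Until these agree, the 80% is not attached to a clearly named primary outcome.

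**Working it through.** **Inputs** (all from Sample size considerations): unexposed rate p1 = 0.08; exposed rate p2 = 0.028; k = 5 exposed per unexposed; two-sided alpha 0.05, so z = 1.960; power 80%, so z = 0.842; difference 0.08 − 0.028 = 0.052.

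**Formula** (pooled two-proportion, no continuity correction), for the size of the smaller arm:

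n = [1.960·√(p̄(1−p̄)(1+1/k)) + 0.842·√(p1(1−p1) + p2(1−p2)/k)]² / (p1−p2)², with p̄ = (p1 + k·p2)/(1+k).

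**1. Reproducing the stated figure.** It comes back when the rates are exchanged (2.8% in the small arm, 8% in the large arm):
- p̄ = (0.028 + 5×0.08)/6 = 0.0713
- first term 0.5526, second term 0.1723
- n = (0.5526 + 0.1723)²/0.052² = 194.4

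Rounded to the nearest whole number this is 194, and 5 × 194 = 970. Power at 194/970 with exchanged rates is 79.9%, which matches the claimed 80%.

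**2. The rates in the arms the protocol gives them.**
- p̄ = (0.08 + 5×0.028)/6 = 0.0367
- first term 0.4035, second term 0.2366
- n = (0.4035 + 0.2366)²/0.052² = 151.5

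This is 152 unexposed and 5 × 152 = 760 exposed, 912 in total, with power 80.1%. With continuity correction it is 174 and 870, 1044 in total.

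**3. Power of the stated 194/970 with the rates in the stated arms.**
- z = (0.052·√194 − 0.4035)/√(0.08×0.92 + 0.028×0.972/5) = (0.7243 − 0.4035)/0.2811 = 1.141
- power = 87.3%; with continuity correction 83.8%; by simulated Fisher's exact test about 86%

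**4. Could another method explain 194 with the rates in the stated arms?**

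| Method (two-sided 0.05, 80% power, 5:1) | Unexposed arm |
|---|---|
| Pooled | 152 |
| Pooled, continuity-corrected | 174 |
| Arcsine | 167 |
| Fisher's exact (simulated) | about 160–170 |
| Log relative risk / log odds ratio | 131 / 135 |
| Unpooled variance | 229 |
| Log-rank events formula (Schoenfeld) | 221–233 |
| Pooled, relative risk exactly 2.8 (7.84% v 2.8%, or 8% v 2.857%) | 160 or 157 |
| Pooled, using the unweighted mean (8% + 2.8%)/2 = 5.4% as p̄ | 192.7, so 193/965 |

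Only the last comes within 1% of 194. It ignores the 5:1 weighting, so it is not the standard formula, but it uses the correct arms.

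**5. Size of the discrepancy.** 1164/912 = 1.28, so the stated total is 28% above the standard result. Against the continuity-corrected 1044, it is 11% above.

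**6. The outcome passages side by side.** Sample size considerations calls stroke primary. The Phase 2 outcomes text can be read as one composite of stroke, thromboembolism and major bleeding, or as a thromboembolic composite with major bleeding as a separate event. The Phase 3 outcomes use similar wording for a thromboembolic composite listed apart from bleeding, which supports the second reading. On either reading, major bleeding is part of the Phase 2 primary outcome and is absent from the outcome that the sample size section calls primary.

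**The case against.** **The error is harmless.** It runs in the safe direction: the stated minimum exceeds what 80% power needs. The section's conclusion, that far more patients will be available than required, holds at 152, 174 or 194 against about 14,000 untreated patients. This stands. A reader might infer that Phase 2 is underpowered or that its feasibility is in doubt, and the documents support neither.

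**The swap is not proven.** A reader might conclude that 194/970 can arise only from exchanged rates. The protocol names no formula, and pooling by the unweighted mean gives 193/965 with the arms as stated. This stands too. Exchange is the best explanation because it returns both arm sizes and the claimed power, but it remains an inference.

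**Aim 4 is still served.** A reader might go further and argue that a composite of benefit and harm would be poorly powered and leave Aim 4 unanswered. The protocol does not support that. It gives no major-bleeding rates from which to compute power for a composite, and the study is expected to far exceed its minimum size. Aim 4 lists stroke, bleeding and death; Selection of comparison groups/controls names the same outcomes; Data/statistical analysis plans hazard ratios for the outcomes of interest; and Plan for addressing confounding speaks of stroke, bleeding or mortality. What remains is a conflict, or at best an ambiguity, over what is primary.

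**The relative risk.** The rates give 8/2.8 = 2.857 and the protocol writes 2.8. This is rounding, and using 2.8 exactly does not recover 194.

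**Conclusion.** The point holds as a minor correction. On the protocol's own inputs, the standard pooled formula requires 152 unexposed and 760 exposed patients (174/870 with continuity correction). The printed 194/970 carries about 87% power (84% with continuity correction), so the size and the power printed together are inconsistent. This rests on the rates sitting in the arms the protocol assigns them and on a standard two-proportion method, since none is named. The cause, most likely exchanged rates, is inferred. The mistake overstates the requirement and changes no decision about whether the study can be done.

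Separately, the sample size section and the Phase 2 outcome text do not agree on the primary outcome and should be reconciled. That is a matter of clarity and does not show that any planned comparison will fail.

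**What to change.** 1. In Sample size considerations, either restate the minimum as 152 unexposed and 760 exposed (912 in total) for 80% power, or keep 194/970 and state about 87% power. In both cases name the formula and say whether a continuity correction is used; with one, the figures are 174/870 (1044) for 80%, or about 84% at 194/970.
2. Align that section with Outcomes to be measured and the Phase 2 outcomes. State that ischaemic stroke/thromboembolism and major bleeding are each analysed with their own hazard ratio, and say which of them the power statement refers to.

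The cost is wording only. No additional patients, data or linkages are needed.

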### **Planned use of linked data and benefit to patients in England and Wales**

For the current study, data linkages to the Hospital Episode Statistic (HES), Office for National Statistics (ONS) death registration data and index of multiple deprivation (IMD) will be required. As the included patients for particular phases will be those eligible for data linkage, then that population will be based on English practices consented to the CPRD linkage scheme. Access to the HES and ONS Mortality data are important aims as we plan to assess the association between patients' outcomes (bleeding events, stroke, and mortality) and OACs prescribing status in NVAF patients. All outcomes will be identified over the course of follow-up through relevant Read/SNOMED codes in patients' electronic records. Stroke or bleeding events will be identified through Read/SNOMED codes in patients primary care records and through linkage to inpatient HES ICD-10 codes in case of hospitalization secondary to stroke or bleeding. ONS data will be used to ascertain specific causes of death (i.e. bleeding related, cardiovascular, or all-cause death), according to ICD-10 codes. While both practice and patient level IMD data will be used to describe OACs prescribing status in terms of level of social deprivation (IMD quintiles), and as covariates in the regression models to be tested across all three phases. By using linked database that include access to longitudinal information on diagnoses, symptoms, laboratory tests, and mortality records, we will be able to thoroughly explore and compare the different outcomes associated with prescribing OACs in NVAF patients. Such information would help to inform guidelines and optimise treatment decisions of OACs for patient with NVAF.

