**Practice level (UK)**

Practice Level Index of Multiple Deprivation

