**Covariates:**

- Patients' demographic information (age, gender, ethnicity, body mass index (BMI), geographic location (rural vs. urban), smoking status, alcohol consumption, Charlson comorbidity index for the severity of comorbidity (Appendix 4), electronic frailty index (eFI), and the index of multiple deprivation (IMD).
- For the sub-group of patients with NVAf and history of cancer, cancer diagnosis will be assessed at the index date of NVAf diagnosis and classified by cancer type into breast, prostate, colorectal, haematological, lung, and other types, and by cancer metastasis status.
- Drugs that affect either stroke or bleeding, or commonly interact with OACs, such as antihypertensive drugs, statins, antiarrhythmics, antidiabetic drugs, anticonvulsants, non-steroidal

anti-inflammatory drugs, corticosteroids, systemic azoles, HIV protease inhibitors and ciclosporin. (Appendix 2).

- The CHA2DS2-VASc stroke risk score that consists of 9 points, one for each of: congestive heart failure (CHF), hypertension (HTN), age  $\geq 75$  years (x 2 points), diabetes mellitus (DM), prior stroke or transient ischemic attack (TIA) or thromboembolism (x 2 points), vascular disease, age 65 to 74 years, and sex category. Information included in the CHA2DS2-VASc score will be identified using Read codes (Appendix 3 and 4), except for age and sex, to build the score and assess the risk of stroke for all included patients in the cohort. Further categorization of eligibility for OACs will be carried according to individual CHA2DS2-VASc scores; “not eligible for OAC” if CHA2DS2-VASc score = 0 in males, or 1 in females; and “OAC eligible” if CHA2DS2-VASc score  $\geq 1$  in males, or  $\geq 2$  in females.

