## **Data/statistical analysis**

1. Phase 1 - NVAF cohort: Annual and crude incidence rates of NVAF cases will be calculated and expressed as person-time at risk with 95% confidence intervals (95% CI). Incidence rates will be calculated by dividing the number of new diagnosed NVAF cases each year by the total population at risk during the same year. NVAF incidence in each calendar year of the study period (2009-2018) will be stratified by age and further standardized by age and deprivation quantiles. Status of anticoagulation therapy will be classified as either OAC prescribed or OAC not prescribed. OAC prescribed patients are those who received prescriptions for OACs during the study period. Treatment patterns for OAC users will be evaluated for OACs continuation, discontinuation or switched). OACs not prescribed will be defined as no prescription record of an OACs at any time after NVAF diagnosis, this will also include patients prescribed lone antiplatelet therapy. Proportions of patients prescribed antiplatelets will be described for both OACs prescribed and not prescribed patients. Baseline demographic, and clinical characteristics, and status of cancer diagnosis across OACs prescribed and not prescribed groups will be presented as number and percentage, mean $\pm$  (SD), or median (interquartile range), as appropriate. For both groups' eligibility for OACs will be described and categorized based on stroke risk according to CHA2DS2-VASc score. Trends in OACs initiation, switching from antiplatelet only to OACs, and from VKA to NOAC will be explored for each year and further stratified by eligibility for OACs and deprivation quantiles. To identify variables independently associated with OACs prescribing multivariate logistic regression models will be used and fitted with the covariates described in section N. Similarly, in a separate analysis for patients with NVAF and previously diagnosed cancer multivariate logistic regression models will be fitted to explore variables independently associated with OACs prescribing (i.e, cancer types and metastasis status). The level of statistical significance was set at  $P < 0.05$ .

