2. Phase 2 – Comparative study: For comparison of demographic variables and comorbidities among OACs treated and not treated individuals, independent sample t tests will be used for numeric variables, while Chi squared  $\chi^2$  tests or Fisher exact tests will be used for categorical variables. To control for imbalances in patient characteristics between cohorts, we will calculate an exposure-specific propensity score as the predicted probability of receiving OACs conditional upon individuals baseline covariate (as described in section M) using logistic regression models. Then we will consider applying propensity score matching methods to match each OACs unexposed controls to up to 5 NVAF OACs exposed cases using a calliper of 0.2 standard deviation (SD) of the propensity score logit. After matching, Cox regression will be used to compute hazard ratios (HRs) of the outcomes of interest, comparing exposure to OACs versus no OACs. Initially crude HRs will be obtained, then stratified by type of OACs (i.e., VKAs and NOACs) and adjusted for age, and other important covariates described in section N. In this phase immortal time bias would occur due to the definition of exposure, where in the time from AF diagnosis till receipt of OACs those in the “OACs prescribed group” cannot have the outcome by design, otherwise they would have been classified as non OAC users. To avoid the problem of immortal time bias, we will consider using time-varying exposures, where in a survival analysis, the time period previous to the index date of OACs initiation is reclassified as nonuser for those in the “OACs prescribed group”.

3. Phase 3 – Major bleeding events cohort: At first, we will use descriptive statistics to present the overall characteristics of this cohort who have experienced major bleeding events while taking OACs. After that patients will be divided to 2 groups one for the patients who resumed anticoagulation after the index major bleeding event and the other for the group who remained OACs free and will compare the patient characteristics between the two groups using Chi squared  $\chi^2$  tests, Fisher's exact tests, and analysis of variance, as appropriate. Survival (time-to-event) models will be constructed to compare the time between the indexed major bleeding to the earliest event of stroke, bleeding, or all-cause mortality considering if patients were restarted on OACs or not. In Cox models we will control for age, time to OACs resumption, CHA2DS2-VASc

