### **Plan for addressing confounding**

In phase 2, we aim to conduct a comparison between NVAF patients who were exposed to OACs (cases) and patients who were not exposed to OACs (controls). We will calculate an exposure-specific propensity score as the predicted probability of receiving OACs conditional upon the effect of potential confounders (described in section M). Then we will use a propensity score matching method to achieve similarity of measured confounders across cases and control groups. When estimating HRs using Cox regression models for the outcomes of interest among patient groups, we will also adjust for age, sex, IMD, stroke risk, bleeding risk, frailty, Charlson comorbidity index, and prescription of antiplatelets.

In phase 3, when looking at the predictors of restarting OACs after the indexed bleeding events we will take in account many confounders that could influence this decision, this will be done by using a multinomial logistic regression to adjust for the covariates described in section N. These covariates will also be considered when conducting survival analysis to compare the time between the indexed major bleeding to the earliest event of stroke, bleeding, or death among patients who restarted OACs and those who did not. Also, when evaluating the outcomes of restarting OACs we will consider the timing of restarting anticoagulation after bleeding, and stratify patients based on different time periods of OACs reinitiating.

In both phase 2 and 3, an additional analysis will be considered to assess the robustness of results to unmeasured confounding using the E-value methodology. This estimates what the relative risk would have to be for any unmeasured confounder to overcome the observed association of OACs prescribing with the clinical outcomes of stroke, bleeding, or mortality.

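### Practice-level deprivation enters patient-level regressions that make no allowance for practice, so its standard errors in the Phase 1 prescribing models would be too small

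*Protocol*

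**What the plan says.** The linked-data section of the protocol states: "While both practice and patient level IMD data will be used to describe OACs prescribing status in terms of level of social deprivation", and adds that these data will serve "as covariates in the regression models to be tested across all three phases". The data request lists the "Practice Level Index of Multiple Deprivation" as a separate item from the patient-level index.

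For Phase 1, Data/statistical analysis says that, to find variables independently associated with anticoagulant prescribing, "multivariate logistic regression models will be used and fitted with the covariates described in section N". The same paragraph ends "The level of statistical significance was set at" P<0.05. The Phase 1 covariate list names IMD without saying at which level.

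For Phase 2 the text reads: "After matching, Cox regression will be used to compute hazard ratios (HRs) of the outcomes of interest". The confounding plan adds that "we will also adjust for age, sex, IMD, stroke risk, bleeding risk, frailty, Charlson comorbidity index, and prescription of antiplatelets".

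None of the covariate lists, the comparison-group section, the analysis section or the confounding plan contains a practice identifier, a practice random or fixed effect, a stratum by practice, or a cluster-robust variance.

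**The concern.** A covariate that is constant within a practice carries information at the level of practices, not patients. The outcome in the Phase 1 models is a prescribing decision, which may differ between practices for reasons unrelated to deprivation. If it does, a single-level logistic model with its default standard errors counts every patient as a separate piece of evidence on practice-level IMD and overstates the precision of that coefficient.

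This bears on a declared aim. Specific aim 3 is to assess factors associated with not prescribing anticoagulants, and socioeconomic status is among those named. With roughly 120,000 patients the default standard errors will be very small, so chance differences between practices could be reported as a deprivation effect.

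**Working it through.** The protocol states no standard error, design effect, practice count or ICC for this analysis, so it has no figure of its own to reproduce. The check sizes the effect under stated assumptions.

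**Inputs**
- Patients: 120,000 incident cases (protocol, Feasibility counts; a count from CPRD GOLD only).
- Significance level: 0.05 (Data/statistical analysis, Phase 1).
- Number of practices: assumed 400 to 1,000, so m = 120,000/1,000 = 120 to 120,000/400 = 300 patients per practice.
- ICC of prescribing within practice: assumed 0.01 to 0.05.

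**Formulae for a covariate constant within practice**
- Design effect: DE = 1 + (m − 1) × ICC.
- Ratio of true to default standard error: √DE.
- Actual two-sided error of a nominal 5% test: 2 × [1 − Φ(1.96/√DE)].

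| m | ICC | DE | √DE | Actual error |
|---|---|---|---|---|
| 120 | 0.01 | 1 + 119 × 0.01 = 2.19 | 1.48 | 19% |
| 120 | 0.02 | 1 + 119 × 0.02 = 3.38 | 1.84 | 29% |
| 120 | 0.05 | 1 + 119 × 0.05 = 6.95 | 2.64 | 46% |
| 300 | 0.01 | 1 + 299 × 0.01 = 3.99 | 2.00 | 33% |
| 300 | 0.02 | 1 + 299 × 0.02 = 6.98 | 2.64 | 46% |
| 300 | 0.05 | 1 + 299 × 0.05 = 15.95 | 3.99 | 62% |

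**Wider assumptions.** With 1,500 practices (m = 80) and ICC 0.005, DE = 1 + 79 × 0.005 = 1.40 and the error is about 10%. With 300 practices (m = 400) and ICC 0.05, DE = 1 + 399 × 0.05 = 20.95 and the error is about 67%.

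**Simulation.** The set-up was 300 practices of 100 patients, no true effect of any covariate, a random practice effect on the logit scale, and 200 replicates per setting. Monte Carlo standard error at a 5% rate is √(0.05 × 0.95/200) = 1.5 percentage points. The table gives the share of runs with P<0.05.

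| Latent-scale ICC | Practice-level covariate, default SE | Practice-level covariate, clustered SE | Patient-level covariate, default SE | Patient-level covariate, clustered SE |
|---|---|---|---|---|
| 0.01 | 13.5% | 5.5% | 5.0% | 4.0% |
| 0.03 | 28% | 4.5% | 5.0% | 5.5% |
| 0.05 | 34% | 4.0% | 6.0% | 6.5% |

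At m = 100 the formula gives 16%, 33% and 42% for the same three ICC values. It runs somewhat higher than the simulation because the simulated ICC is on the latent scale. Direction and order of size agree.

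The patient-level columns are a favourable case. The simulated covariate was 0.2 times the practice-level one plus independent noise of unit variance, so only 0.04/1.04, about 4%, of its variance lay between practices, and that part was already in the model. They show that inflation can be near zero for patient-level IMD, not that it must be.

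**The case against.** The strongest reply is that the protocol is silent rather than wrong. It never says that patients of one practice are independent or that the variance will be unclustered, and such details are often left to a statistical analysis plan, which is not at hand. This has force: one sentence in such a plan would settle the point. It does not remove the point, because the protocol fixes two things that do not fit together: a practice-level covariate and a model type that, as named, has one level. A random-intercept logistic model is a different model, and the section is specific elsewhere (calliper width, Schoenfeld residuals, software version).

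A second reply is that the size is assumed. That stands. Only the 120,000 comes from the protocol, and it is a GOLD count, whereas the study uses GOLD and Aurum and restricts linked phases to English practices. Phase 1 is also described as hypothesis generating, which lowers the stakes of a false positive without making the interval correct.

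Three stronger readings are tempting and are not supported:
- A reader might infer that all deprivation results are unreliable. Patient-level IMD is also requested and planned, and its error can be close to nominal.
- A reader might infer that practice is a main driver of prescribing and confounds the Phase 2 comparison. The Study background points to age, perceived bleeding risk and earlier bleeding. A practice difference in prescribing confounds only if practice also affects outcome by another route, which nothing in the protocol shows. Hospitalised events and causes of death also come from HES and ONS, which do not depend on practice coding. Practice IMD and rural or urban location would absorb part of any practice difference.
- A reader might infer that practice prescribing level belongs in the propensity model. Such a variable may act like an instrument, amplifying unmeasured confounding and reducing overlap.

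**Conclusion.** The point holds for practice-level IMD, chiefly in the Phase 1 prescribing models. The analysis as written would give standard errors for that term that are too small if prescribing varies between practices. With 120,000 patients, 400 to 1,000 practices and an ICC of 0.01 to 0.05, they would be understated by a factor of about 1.5 to 4, and the false-positive rate would be about 19% to 62% instead of 5%. The practice counts and ICC are assumptions, so the range illustrates the size of the problem and does not estimate it for this study. Other covariates that cluster within practice are affected less, possibly negligibly.

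The reach into later phases is limited. The P<0.05 rule is stated only for Phase 1, and neither the Phase 2 propensity list nor the Phase 3 Cox list names IMD. However, the linked-data section claims IMD for all phases and the confounding plan adjusts the Phase 2 Cox model for it, so the same care is needed wherever practice-level IMD is used. This should be corrected; it does not undermine the study's main comparisons.

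**What to change.** In Data/statistical analysis, Phase 1, state that the prescribing models will use standard errors clustered on practice or a practice random intercept. Name patient-level IMD as the main deprivation variable in the covariate list, and enter practice-level IMD only in models that account for practice. Say that any Phase 2 or Phase 3 model that includes practice-level IMD will also use practice-clustered standard errors. If a statistical analysis plan already specifies this, a cross-reference is enough.

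The change is small: a few lines of code and no new linkage. The cost is wider confidence intervals, mainly for practice-level IMD.
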